## Abstract

**Background:**

Hypertension is a major contributor to various adverse health outcomes. Although previous studies have shown the benefits of home blood pressure (BP) monitoring over office-based measurements, there is limited evidence comparing the effectiveness of whether a BP monitor integrated into the electronic health record is superior to a nonintegrated BP monitor.

**Objective:**

In this paper, we describe the protocol for a pragmatic multisite implementation of a quality improvement initiative directly comparing integrated to nonintegrated BP monitors for hypertension improvement.

**Methods:**

We will conduct a randomized, comparative effectiveness trial at 3 large academic health centers across California. The 3 sites will enroll a total of 660 participants (approximately n=220 per site), with 330 in the integrated BP monitor arm and 330 in the nonintegrated BP control arm. The primary outcome of this study will be the absolute difference in systolic BP in mm Hg from enrollment to 6 months. Secondary outcome measures include binary measures of hypertension (controlled vs uncontrolled), hypertension-related health complications, hospitalizations, and death. The list of possible participants will be generated from a central data warehouse. Randomization will occur after enrollment in the study. Participants will use their assigned BP monitor and join site-specific hypertension interventions. Cross-site learning will occur at regular all-site meetings facilitated by the University of California, Los Angeles Value-Based Care Research Consortium. A pre- and poststudy questionnaire will be conducted to further evaluate participants’ perspectives regarding their BP monitor. Linear mixed effects models will be used to compare the primary outcome measure between study arms. Mixed effects logistic regression models will be used to compare secondary outcome measures between study arms.

**Results:**

The study will start enrolling participants in the second quarter of 2023 and will be completed by the first half of 2024. Results will be published by the end of 2024.

**Conclusions:**

This pragmatic trial will contribute to the growing field of chronic care management using remote monitoring by answering whether a hypertension intervention coupled with an electronic health record integrated home BP monitor improves patients’ hypertension better than a hypertension intervention with a nonintegrated BP monitor. The outcomes of this study may help health system decision makers determine whether to invest in integrated BP monitors for vulnerable patient populations.

**Trial Registration:**

ClinicalTrials.gov NCT05390502; clinicaltrials.gov/study/NCT05390502

**International Registered Report Identifier (IRRID):**

PRR1-10.2196/45915

## Introduction

Hypertension is a marked modifiable risk factor for many adverse health outcomes, with the highest attributable risk for cardiovascular disease and death [1]. About half of the US adult population has hypertension, with the majority having uncontrolled hypertension [2]. The inadequate treatment of hypertension for certain groups is a large source of health disparities [3]. Clinically, the diagnosis of hypertension is made using office-based blood pressure (BP) measurements at several week intervals [4] and confirmed with an out-of-office reading or using ambulatory BP monitoring [5,6], as there is growing evidence showing differences in BP measurements in the office compared to the home setting [7,8]. Variations in adherence to clinical guidelines on how to properly perform BP readings, patient anxiety, environmental factors, and “white-coat hypertension” all contribute to these differences [6,9]. Additionally, many studies have shown the superiority of home BP monitoring compared to office BP monitoring in terms of cardiovascular and renal outcomes, all-cause mortality [1,8,10,11], and patient empowerment and adherence to medical therapies for hypertension [12].

Although the benefits of home BP monitoring compared to office-based monitoring are well studied, optimal methods for obtaining home BP readings are less clear. A previous study showed improvements to systolic BP at 1 year after a self-monitoring and digital intervention involving a health care provider-managed lifestyle modification and medication titration approach compared to usual care [7]. Whereas a single-center study found no difference in BP change using an electronic health record (EHR)–connected smartphone device to record BP using a standard self-monitoring strategy [13]. This randomized, comparative effectiveness trial adds to the existing literature by including multiple sites and comparing an EHR-integrated monitor with automated BP data uploads to a standard self-monitoring approach.

In developing the protocol for this study, we used the eHealth Enhanced Chronic Care Model (eCCM) [14] to shape our theoretical understanding that remote BP monitoring can improve patients’ and health care providers’ “wisdom” [15,16] to provide interventions capable of improving hypertension control. This project aligns with a joint scientific advisory on hypertension control from the American Heart Association, the American College of Cardiology, and the Centers for Disease Control and Prevention, which argued for systems-level, population-health-level initiatives to control hypertension, involving the community around a patient, leveraging data from EHRs, and patient-provider engagement [17].

This manuscript was developed to describe the protocol for this pragmatic multisite study that evaluates whether an integrated BP monitor performs better at controlling hypertension than a self-reporting strategy. We define the roles and responsibilities of key partners, study design, key outcomes, and statistical analyses.

## Methods

### Setting and Study Design

The University of California (UC) Health System is a large academic health system serving a diverse patient population throughout California, the United States, and internationally. It includes teaching hospitals, affiliations with community health clinics, health professional schools, research centers, and other health care entities. This study protocol describes a randomized, comparative effectiveness trial that will be conducted at 3 of the UC Health System sites (UC Davis [UCD], UC Los Angeles [UCLA], and UC San Francisco [UCSF]). Figure 1 describes the general timeline. Enrollment will occur over 6 months after study initiation, and each participant will be followed for 6 months after enrollment.

**Figure 1 figure1:**
[figure not shown]
Timeline for the study. Participants will be followed for 6 months after enrollment date. BP: blood pressure; IRB: institutional review board.

### Defining Key Partners and Study Preparation

The UCLA Value-Based Care Research Consortium (VBCRC) will lead the planning, implementation, and evaluation of this study in collaboration with the UCLA Department of Medicine Statistics Core, the UC Office of the President (UCOP), and each UC site. The UCLA VBCRC is a team that aims to improve value in health care through partnerships with health systems and researchers. The UCOP team will provide input into study design and feasibility, as well as funding for the study, including the BP monitors. Each UC site will have a designated site champion, program manager, and IT lead (Multimedia Appendix 1 details the responsibilities of these roles). The UCLA VBCRC team will facilitate regular meetings with representatives from each team, focusing on cross-site learning, troubleshooting implementation issues, and providing updates on progress. Further evaluation of cross-site variations, barriers to implementation, and understanding of patient experiences will be obtained from qualitatively coding and analyzing these regularly scheduled meetings with the sites.

In preparation for the study, the UCLA VBCRC met with a community action board consisting of representatives from community organizations serving large numbers of diverse members with hypertension to understand patient concerns and perspectives regarding this study. Overall, the community action board supported the need for this project but raised concerns regarding proper training for using the BP monitors for participants in the study. They also reiterated the importance of providing instructional materials at various education and literacy levels, as well as individualized support for participants when needed. This feedback was provided to the sites and the BP monitor company.

### Site-Specific Hypertension Interventions

In addition to following core protocol instructions, each site will design and implement a hypertension intervention for both arms of the study. The study sites are given the autonomy to create their own site-specific hypertension intervention to fit their patient population needs and available resources. Table 1 compares interventions across each UC site, including whether the intervention is web-based only or hybrid (component of in-person and web-based), the main health care providers involved in the intervention, specific details about the intervention, discharge criteria from the program, and site-specific inclusions and exclusions.

**Table 1 table1:** Comparison of site interventions.

	University of California, Davis	University of California, Los Angeles	University of California, San Francisco
Web-based only, hybrid (in-person and web-based)	Hybrid	Web-based only	Hybrid
BP^a^ monitor distribution plan (eg, mail, in person, etc)	Mailed directly to the patient	Mailed directly to the patient	Mailed directly to the patient
Main providers involved in the intervention	Pharmacist	Pharmacist Patient service representative Primary care provider Program supervising physician	Pharmacist Primary care provider Health care navigator
General structure of study arms	Intervention: EHR^b^ integrated remote BP monitor with pharmacist follow up Control: nonintegrated BP monitor with pharmacist follow up	Intervention: EHR integrated remote BP monitor + web-based patient portal Control: nonintegrated BP monitor + web-based patient portal	Intervention: EHR integrated remote BP monitor + usual care and follow-up Control: nonintegrated BP monitor + usual care and follow-up
Frequency of BP checks	There is no minimum per month. Ideally, at least 16 per month.	There is no minimum per month. Ideally, at least 16 per month.	There is no minimum per month; however, patients will receive daily reminders. Ideally, at least 16 per month.
Site-specific intervention	Initial visit (60 minutes): (1) The pharmacist will provide disease management (ie, monitor BP readings and help titrate medications accordingly). (2) Notify the PCP^c^ of patient participation or access to monitor. Clinic visits (1 minimum): (1) Before the pharmacist’s intervention. (2) As needed to facilitate care plans and achieve BP goals	Initial visit (40 minutes): (1) Review: PMH^d^ relevant to treatment, calculate 10-year ASCVD^e^ risk, labs, current BP management, diet and exercise, medication adherence, access to a home BP monitor, and BP measurement techniques. (2) Treatment: develop an individualized treatment plan, including starting antihypertensive medications, hypertension education, lifestyle management, and reviewing BP measurement techniques. (3) Communication: send a visit summary to PCP. (4) Visits performed by pharmacists or supervising program physicians. (5) Schedule: next visit in 2-4 weeks (monthly follow-up). Follow-up visit (20 minutes): review the individualized treatment plan, home BP measurements, and access to medications (if any).	Initial visit (40 minutes): (1) Review: PMH relevant to treatment, current blood pressure management, diet and exercise, labs, medication adherence, access to a home BP monitor, and BP measurement techniques. (2) Treatment: create an individualized plan that may include starting a new antihypertensive, dose adjustment, or tapering medications contributing to high BP, and set or reinforce target BP goals. (3) Schedule: next visit in 4 weeks. (4) Visits performed by a pharmacist, primary care doctor, nurse practitioner, or registered nurse. Follow up: every 1-2 months.
Control group	Self-report BP. Intervention is the same as above.	Self-report BP. Intervention is the same as above.	Self-report BP. Intervention is the same as above.
Discharge from the program	BP at goal for 2 consecutive visits Resistant hypertension criteria Clinical concerns develop, for example, recurrent orthostatic symptoms with systolic BP <100 mm Hg, persistent changes in labs (electrolytes and GFR^f^), significant excursions in BP after confirming measurement technique, and unstable symptoms BP is above goal after 6 months The patient requests discharge	BP at goal for 2 consecutive visits Resistant hypertension criteria Clinical concerns develop, for example, recurrent orthostatic symptoms with systolic BP <100 mm Hg, persistent changes in labs (electrolytes and GFR), significant excursions in BP after confirming measurement technique, unstable symptoms BP is above goal after 6 months The patient requests discharge	BP is well controlled. Patient request or lost to follow-up. Complicating comorbid conditions develop
Site-specific inclusion criteria	None	The participant must be active on the web-based patient portal.	The participant must be active on the web-based patient portal.
Site-specific exclusion criteria (if any)	None	None	None

^a^BP: blood pressure.

^b^EHR: electronic health records.

^c^PCP: primary care physician.

^d^PMH: patient medical history.

^e^ASCVD: atherosclerotic cardiovascular disease.

^f^GFR: glomerular filtration rate.

### Eligibility, Inclusion, and Exclusion Criteria

A complete list of eligibility, inclusion, and exclusion criteria is listed in Textbox 1. Eligible participants must be 18 years of age or older, willing and functionally able to use the BP monitor, and have access to the web-based health care patient portal (with help from another person if needed). Participants will be included if they have had an outpatient visit within the last year and 2 readings of systolic BP ≥140 mm Hg or diastolic BP ≥90 mm Hg within 6 months of each other, have a primary care physician within the health care system, and are taking three or fewer antihypertensive medications. There is no language preference or maximum age cutoff for this study.

Participants will be excluded if they had a recent BP measurement greater than or equal to 180/110 mm Hg (office BP) or greater than or equal to 175/105 mm Hg (self-monitored BP), have a history of conditions that could lead to refractory hypertension (Textbox 1), are currently incarcerated, are enrolled in home health, hospice, or a hypertension management program, have cognitive impairment that prevents them from participating in intervention activities, or have a white coat hypertension diagnosis. Individuals with BP measurements greater than or equal to 180/110 mm Hg (office BP) or greater than or equal to 175/105 mm Hg (self-monitored BP) will be excluded because they may have treatment-resistant hypertension or may need more intensive intervention than is being provided with this program.

Complete list of eligibility, inclusion, and exclusion criteria.
**Eligibility criteria**
Aged 18 years and older.Must be willing and functionally able (with help from another person if needed) to perform remote blood pressure (BP) monitoring.Have access to the web-based health care portal (with help from another person if needed).
**Inclusion criteria**
Have outpatient visit within the last 12 months, and have a previous visit within 6 months of inclusion outpatient visit with diagnosis of hypertension, defined as having 2 readings of systolic BP >140 mm Hg or diastolic BP >90 mm HgHas at least one visit with primary care physician in prior year.Takes 0 or 3 antihypertensive prescriptions (can include pills with 2 different drugs so could be on 2 medications).
**Exclusion criteria**
BP > 180/110 mm Hg (office) or > 175/105 mm Hg (self-monitored BP measurements)PheochromocytomaUncontrolled hypothyroidism or hyperthyroidismRenal artery stenosisConn’s syndromeEnd Stage Renal Disease (ESRD)Chronic Kidney Disease (CKD) Stage 3b (CrCL <45) and worseTransplant patients—used the code that if they ever had a transplantPregnancySevere aortic stenosisHospice or end-of-life or palliative CareLeft Ventricular Ejection Fraction (LVEF) <30%Acute cardiac event in the last 3 months (eg, myocardial infarction)Heart block and arrhythmiasRecurrent or symptomatic hypotension (systolic BP <100 mm Hg or diastolic BP <60 mm Hg)Drug and alcohol abuseOrthostatic hypotension (drop in systolic BP >20 mm Hg)Other secondary causes of hypertensionReceiving hypertension management from other services (home health, hospice, already enrolled in hypertension management program)White coat hypertension

### Enrollment, Randomization, and Study Initiation

Figure 2 describes the study phases, starting with the creation of the potential participant list obtained from the Center for Data-Driven Insights and Innovation (CDi2) and the UC Health Data Warehouse (UCHDW), verification of eligibility criteria, and study enrollment, which we aim to start in the second quarter of 2023. This study plans to enroll 660 participants (about 220 per site and 330 participants in each arm of the study). These power calculation estimates are based on previous literature reviews [18,19] to achieve an 80% power to detect a difference of 0.23 SDs and an anticipated 10% attrition rate. An enrollment script will be provided to each site (Multimedia Appendix 2). Randomization will occur after enrollment using a randomization allocation template within REDCap (Research Electronic Data Capture), a secure web-based platform designed to help capture data and operationalize research studies [20,21].

After enrollment and randomization, participants will receive their BP monitor (integrated or nonintegrated) and complete a prestudy questionnaire (Multimedia Appendix 3). Each UC site will then administer their site-specific hypertension intervention, which will be administered to both arms of the study. At the end of the 6-month follow-up period, a similar poststudy questionnaire evaluating participant experiences will be completed (Multimedia Appendix 4). Given the nature of the different BP management interventions, site representatives and participants will not be blinded to study arm assignments; however, the UCLA VBCRC evaluation team will be blinded.

**Figure 2 figure2:**
[figure not shown]
Study phases. BP: blood pressure.

### Blood Pressure Monitors, Electronic Health Record Integration, and Operations

Both integrated and nonintegrated BP monitors Omron 5 Series Model, BP7250 (Omron Healthcare Inc) will be directly mailed to participants’ homes, and participants will be asked to follow standard instructions for measuring BP.

EHR integration refers to the secure transfer of data from the remote BP monitor to the health system’s electronic medical record through DataHub (Omron). The process of integration will occur in collaboration with site IT leads, Omron representatives, and the Redox (Redox Inc) team. Redox is a backend integration platform that provides a standardized method for receiving and sending data between health care EHR systems and technology vendors such as Omron Healthcare Inc. Though more time- and labor-intensive to implement, the Redox platform allows for the immediate upload of data into the EHR without the use of a mobile app. For all participants with the integrated BP monitor, BP measurements will be immediately available in the EHR for intervention.

In terms of operations, the integrated BP monitors will store measurements in the provided DataHub, which will then automatically transmit BP measurements to Redox. At the backend, these BP measurements in Redox will then be transmitted to the patients’ medical records and stored as a flowsheet item in the EHR that can be acted upon by local site-specific interventions. In contrast, the nonintegrated BP monitor will require participants to self-report BP measurements to their health care provider through the site-specific web-based patient portal. Participant and staff training on how to use the integrated BP monitor, techniques for taking BP, and further technical support in multiple languages will be conducted by Omron representatives. Omron representatives will call the participant after the monitor has been delivered and follow a standardized script that includes asking the participant to take multiple BP measurements and ensuring BP readings are properly captured in the database.

### Primary and Secondary Outcomes

The primary outcome is the difference in BP from baseline compared to 6 months between study groups (integrated vs nonintegrated BP monitor), defined as a continuous measure of BP in mm Hg. Secondary outcomes include a binary measure of controlled versus uncontrolled hypertension (where uncontrolled is defined as systolic BP >130 mm Hg or diastolic BP >80 mm Hg based on American College of Cardiology and American Heart Association Practice Guidelines [22]), hypertension-related health complications by the end of the study, including acute coronary syndrome (myocardial infarction), stroke (ischemic and hemorrhagic), decompensated heart failure, syncope, electrolyte abnormalities (hyponatremia, hypokalemia, and hyperkalemia), hospitalization, and mortality (all-cause). Hypertension-related health complications will be captured using International Classification of Diseases Ninth or Tenth Revision codes after the participants have started the study.

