### Statistical Analysis

For the primary outcome, linear mixed effects models will be used to compare changes from baseline home BP to 6 months from enrollment between the integrated and nonintegrated remote monitoring arms of the study. Models will include random site effects to account for the clustering of patients within sites. Models will adjust for demographic and clinical characteristics including age, sex, race, and ethnicity, as well as social vulnerability (the census tract Social Vulnerability Index). The evaluation of each arm will be based on a Wald test of the primary model term, and estimated differential changes will be reported along with a 95% CI. For the dichotomous secondary outcomes, we will use mixed effects logistic regression models with similar specifications and report differences in terms of odds ratios. A significance level of .05 will be used, and all analyses will follow the intention-to-treat principle. For patients who do not have a BP reading at 6 months, we will use the reading closest to 6 months, with a minimum 2-month period between the baseline and final reading [23,24]. Missing data will be handled through multiple imputations using pattern-mixture models. For the exploratory pre-post analysis, we will use linear mixed effects models to evaluate changes in BP. The analysis will be performed using SAS (version 9.4; SAS Institute Inc).

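### The adjusted mixed logistic model set for every binary secondary outcome does not suit the probably rare clinical events, and the complications heading mixes cardiovascular events with possible treatment harms

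*Protocol article*

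**What the plan says.** Under Primary and Secondary Outcomes, the protocol article names blood pressure control as a binary secondary outcome. It then gives a heading for hypertension-related complications that covers acute coronary syndrome, stroke and decompensated heart failure and continues with "syncope, electrolyte abnormalities (hyponatremia, hypokalemia, and hyperkalemia), hospitalization, and mortality (all-cause". These events are to be captured from diagnosis codes.

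Under Statistical Analysis: "For the dichotomous secondary outcomes, we will use mixed effects logistic regression models with similar specifications and report differences in terms of odds ratios". The specifications described for the primary model are a random site effect and adjustment for age, sex, race, ethnicity and the Social Vulnerability Index. The same section says "A significance level of .05 will be used". No binary outcome is exempted or labelled descriptive.

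Under Setting and Study Design, "each participant will be followed for 6 months after enrollment". The only power statement, under Enrollment, Randomization, and Study Initiation, is that the sample was chosen "to achieve an 80% power to detect a difference of 0.23 SDs and an anticipated 10% attrition rate". That is an effect on a continuous scale.

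In Table 1 (Site-Specific Hypertension Interventions), the discharge criteria at UC Davis and UCLA include, as clinical concerns that may develop, recurrent orthostatic symptoms with low systolic pressure and "persistent changes in labs (electrolytes and GFR". The UCSF column has neither item.

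**The concern.** There are two linked problems.

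**Method.** Heart attack, stroke, decompensated heart failure and death over about six months in 660 people are likely to be few. A model with a treatment term, five named covariates and a random site effect needs far more events than that. With an empty arm, the maximum likelihood odds ratio is zero or infinite. With a handful of events, the estimate is unstable and the interval so wide that it excludes almost nothing. A reader shown an adjusted odds ratio with p above .05 could take it as evidence that integration does not affect clinical events.

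**Label.** Syncope and disorders of sodium and potassium are listed as complications of hypertension. Both arms have an intervention in which medication may be started or adjusted, so these events may also be effects of treatment. Under one heading they sit beside events that better control should reduce. The two groups could move in opposite directions, and a rise in harm would be reported under a label that suggests disease.

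**Working it through.** **The plan's own figure.** Inputs from the article: 0.23 SD, 80% power, significance level .05 (taken as two-sided), 10% attrition.

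n per arm = 2 × (1.960 + 0.842)² / 0.23² = 15.70 / 0.0529 ≈ 297; 297 / 0.90 = 330; total 660. This reproduces the plan and is sound for the primary outcome. It says nothing about binary events.

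**Rare events.** The article gives no event rate, so the six-month risk p for one event type is assumed and varied. I use all 330 per arm: events come from coded records under intention to treat, so a missing blood pressure reading need not remove a participant.

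- Expected events per arm = 330p
- P(a given arm has none) = (1 − p)^330
- P(at least one arm has none) = 1 − [1 − (1 − p)^330]²
- SE of log OR at a true OR of 1 = √{2 × [1/(330p) + 1/(330(1 − p))]}; 95% limits = exp(±1.96 × SE)

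| Assumed risk | Events per arm | P(given arm empty) | P(at least one arm empty) | 95% CI around OR = 1 |
|---|---|---|---|---|
| 0.25% | 0.8 | 0.438 | 68% | 0.05 to 21 |
| 0.5% | 1.7 | 0.191 | 35% | 0.11 to 8.7 |
| 1% | 3.3 | 0.036 | 7% | 0.22 to 4.6 |
| 3% | 9.9 | below 0.001 | below 0.1% | 0.41 to 2.4 |

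Example at 1%: SE = √{2 × [1/3.3 + 1/326.7]} = 0.78; exp(±1.53) = 0.22 to 4.6. The normal approximation is itself poor in the first rows, so those limits show only scale.

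With 297 per arm, the empty-arm chance is 73% at 0.25% and 40% at 0.5%.

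**Events against model terms.** At 1% there are about 6.6 events in both arms together. If the covariates carry over as the plan's wording suggests, there are at least six fixed-effect coefficients besides the intercept (arm plus five covariates), or about one event per coefficient. With three equal sites there are 110 participants per arm and site. A cell is empty with probability 0.99^110 = 0.331, so at least one of six is empty with probability 1 − 0.669^6 ≈ 91%. That leaves little information on variation between sites.

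**Power for a halving of the odds**, 330 per arm: about 6%, 8% and 11% at 0.25%, 0.5% and 1%, and 25% at 3%.

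**More frequent outcomes.** At an assumed control risk of 15% or 20%, power for OR 0.5 is 79% or 89%; for OR 0.7 it is 33% or 41%.

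**If the listed items were pooled** (assumed control risks 1% cardiovascular and 4% syncope or electrolyte, independent):

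- Control risk = 1 − 0.99 × 0.96 = 0.0496.
- Risk ratios 0.8 and 1.05: 1 − 0.992 × 0.958 = 0.0497, pooled OR 1.00.
- Risk ratios 0.8 and 1.25: 1 − 0.992 × 0.950 = 0.0576, pooled OR 1.17.

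So a cardiovascular benefit could vanish or appear as harm. This shows direction only: 16.4 against 19.0 expected events gives a 95% CI of about 0.6 to 2.3 around 1.17.

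**The case against.** These are secondary outcomes, the article claims no power for them, and the trial's stated aim is improvement of blood pressure. A condensed article may leave the handling of sparse data and the grouping of events to a fuller document. Every event rate above is assumed. Events are counted to the end of the study, so with six months of enrollment the earliest participants could contribute up to about 12 months.

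Much of this stands, and it limits the point. Lack of power for secondary outcomes is not in itself a fault. Longer capture does not rescue the rare events, however: doubling a 1% risk to 2% gives 6.6 events per arm and about 18% power for OR 0.5. The point also does not rest on an omission. The article positively states one modelling rule for all binary secondary outcomes, at a .05 level, and positively places syncope and electrolyte disorders under the complications heading.

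A reader might infer more than the text supports:

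- **That the events form one composite.** None is defined. The abstract lists complications, hospitalizations and death separately, and the analysis section speaks of outcomes in the plural.
- **That the population is low risk.** The exclusions remove recent acute cardiac events, severe left ventricular dysfunction and the highest pressures, but there is no upper age limit and older cardiovascular disease is not excluded.
- **That the protocol itself classes these events as drug harms at all sites.** The orthostatic and electrolyte items appear for two of three sites, as clinical concerns not attributed to treatment, and syncope is not named there. Both arms receive the same site intervention, so a rise under integration is possible but not established.

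**Conclusion.** The point holds in a limited form. For individual rare events, the stated model would often be unstable or not estimable. At assumed six-month risks of 0.25% to 1%, the trial expects about 0.8 to 3.3 events per arm, with a 68% to 7% chance of an empty arm. Where an odds ratio can be estimated, it is too imprecise to support a conclusion of no effect. Separately, the heading mixes cardiovascular complications with events that may be treatment harms, and the text does not settle whether it is one outcome or several.

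It would go too far to say that the secondary objective cannot be answered at all. Blood pressure control is unaffected. A more frequent outcome, possibly hospitalization, could show a large effect (OR about 0.5) if its risk were 15% to 20%. The size of the problem rests on assumed rates, but even at 3% power for a halving of the odds is only about 25%. The primary outcome and its sample size are not in question.

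**What to change.** **Primary and Secondary Outcomes.** List two groups: cardiovascular complications (acute coronary syndrome or myocardial infarction, stroke, decompensated heart failure) and safety events (syncope, hyponatremia, hypokalemia, hyperkalemia). Keep hospitalization and all-cause death as separate outcomes. State that the first two groups will not be pooled.

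**Statistical Analysis.** Keep mixed effects logistic regression for blood pressure control and for outcomes with enough events, for example hospitalization if it proves frequent. For sparse events, report counts by arm and risk differences with exact confidence intervals, or Firth logistic regression with arm and site only, and label these results descriptive. State that the trial is not powered to conclude that integration has no effect on clinical events.

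**Cost.** Changes of wording and slightly more programming, with no new data. The trial gives up a formal adjusted test for rare events, which would have been uninformative.
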